# Study Design

## Study site

Ndirande is a peri-urban hillside township adjacent to Blantyre, the largest city in Malawi. Accurate census data are not available for Ndirande, but the population is approximately 200,000. Malaria transmission is year-round, with a seasonal peak from December to March corresponding to the rainy season. The Ndirande Health Centre is the sole government health facility serving the entire township, and consists of a complex of buildings with outpatient clinics and a maternity center. Our field team of clinicians, nurses and technicians has been conducting malaria drug efficacy studies at the Health Centre continuously since 1997 and has an excellent relationship with the community. During this time more than 3,000 participants have been enrolled in five studies, including clinical trials and longitudinal studies. After operating in dedicated space within the Centre facility for several years, in 2002 we established a new research facility on the Centre grounds. The Blantyre Malaria Project Research Clinic contains rooms for clinicians and nurses, laboratory space for the microscopists, a dispensary, an administrative office, a conference room and a computer room for real time data entry. We maintain a close relationship with the Ndirande Health Centre government workers. When we provide diagnosis and treatment in the context of our clinical studies, we offer relief from overcrowded conditions in the Centre. Back-up clinical and laboratory support is available a 10 minutes drive from the Centre at the pediatric research ward in Queen Elizabeth Central Hospital.

## Description

This study is a randomized longitudinal open-label drug efficacy trial among children who present to a government health clinic with uncomplicated falciparum malaria. Otherwise healthy children who are found to have malaria and whose parents/guardians consent to participate in the study will be enrolled in this study for one year. The participants will be randomized to one of the four drug treatment arms: CQ monotherapy, CQ plus artesunate, CQ plus azithromycin, and CQ plus AP. They will continue to receive the same treatment for each new episode of malaria for the next year. If the treatment fails, participants will receive rescue therapy, but will continue in the trial. At the first diagnosis and all subsequent new episodes of malaria, a 28 day drug efficacy study will be completed. Participants will also be asked to return for routine follow-up visit every four weeks.

***Follow-up.*** With enrollment and the first dose of therapy occurring on day 0, participants will be followed actively on days 1, 2, 3, 7, 14, 21 and 28 at the study clinic, and by daily availability of a study clinician to evaluate and treat as needed even if follow-up is not scheduled. At all active and passive follow-up times, malaria smears, hemoglobin and filter paper strips will be obtained and brief history taken and physical examinations made to seek signs or symptoms of persistent or recrudescent malaria and use of any medications outside the protocol.

In addition, participants will attend four-weekly follow-up visits at the study clinic. Weight, height, hemoglobin, temperature and malaria smears and filter papers for later evaluation of asymptomatic disease will be recorded and the participant examined and questioned for signs or symptoms of malaria or other illnesses. Further evaluation, including immediate reading of the malaria smear, will take place if the parent/guardian reports symptoms, if the participant appears ill to the clinic staff or there is a documented fever. All non-malaria illnesses will be treated according to the national guidelines.

Management of early or delayed attendance of these follow up visits is detailed in the Standard Operating Procedure.

## Definition of treatment outcomes

The 2004 WHO definitions of treatment outcomes will be used as follows:

Therapeutic efficacy will be defined as:

- Early treatment failure (any one of the following)
  - danger signs or severe malaria on days 1, 2 or 3, with parasitemia. Hemoglobin less than 5 without any other signs of severe disease when a participant is receiving therapy will not be a criteria for Early Treatment Failure as hemoglobin levels frequently decrease even with effective therapy.
  - parasitemia on Day 2>Day 0 level
  - axillary temperature > 37.5oC on day 3 in the presence of parasitemia
  - parasitemia on day 3 > 25% of day 0 level
- Late clinical failure
  - development of danger signs, severe malaria or axillary temperature > 37.5oC or a history of fever within the past 24 hours in the presence of parasitemia during days 4-28
  - and no criteria for early treatment failure
- Late parasitologic failure
  - Presence of parasitemia on day 28 without fever
  - and without previously meeting any of the criteria for early treatment or late clinic failure
- Adequate clinical and parasitologic response
  - absence of parasitemia on day 28
  - and without previously meeting any of the criteria of early treatment or late clinical failure

A new episode of malaria will refer to any episode of clinical malaria (symptoms and a positive malaria smear) that occurs more than 14 days after therapy.

If a seizure meets the following criteria of a febrile seizure, the episode will not be considered a danger sign. The following criteria must be met:

1. Occurring in the presence of a reported or documented fever or with a rise in temperature.
2. Generalized seizure witnessed by reliable family member or study staff
3. Duration ≤30 minutes
4. Absence of mental status impairment two hours after the event..
5. Normal neurological examination by a study clinician or investigator within 24 hours of seizure.

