## Follow-up

Follow-up visits may be one of four types: day of new malaria episode diagnosis, drug efficacy follow-up, routine visit, unscheduled visit.

On the initial day of a new diagnosis, a venipuncture will be performed to obtain the following studies: filter paper sample for molecular analysis, CBC, ALT, creatinine, chloroquine level and specimen for cryopreservation of parasites. The total volume will be approximately 3.5-5 mL.

Drug efficacy follow-up occurs after the initial and all subsequent administrations of the study drug to treat symptomatic malaria. Visits will occur on days 1, 2, 3, 7, 14, 21, 28. Hemoglobin, malaria smears and filter papers will be obtained on each of those days and a physical examination will be completed. Specimens from a finger prick will be obtained on two occasions after day 0: on day 14 and an additional day assigned randomly at enrollment. Chloroquine level, CBC, ALT and creatinine will be measured routinely on day 14, after acute changes associated with malaria should have resolved If the participant misses the visit corresponding to the day a chloroquine level and/or CBC, ALT and creatinine arescheduled to be collected, the study team will endeavor to collect this specimen as the next visit. Drug administration will occur on days 1 (2nd dose) and 2 (3rd dose).If treatment failure occurs after day 3 and the parasite density is >10,000/mm3, blood will be collected to measure the chloroquine level and for cryopreservation of malaria parasites for further in vitro susceptibility testing. A neurologic exam will occur on day 28.

Routine visits occur every four weeks. Malaria smear and filter paper will be obtained. The malaria smear will be read at that time only if there are complaints of an illness or the clinician suspects malaria. The encounter will include an interval history, questions about off-study drug use, recent travel, bed net use and a physical examination. At routine visits 4, 8 and 13, CBC, ALT and creatinine will be obtained for safety monitoring surveillance. All blood specimens will be collected from a finger prick except for the specimens for cryopreservation which require 3-5 ml. On all other days, the amount of blood drawn from the finger prick will range from 0.05 ml (malaria smear, hemoglobin, filter paper) to approximately 0.5 ml (malaria smear, hemoglobin, filter paper, CBC, ALT, creatinine and chloroquine level).

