## Molecular analysis

Molecular analysis of parasite DNA will be performed in batches and results will not be available for clinical application. Wild-type chloroquine susceptible parasites are distinguished from mutant chloroquine resistant parasites by nested-PCR followed by allele specific restriction digest, following standard procedures available on our Website: <http://www.medschool.umaryland.edu/cvd/[name].asp>.

Cases of parasitemia from day 14 through day 28 will undergo MSP-2 genotyping following the protocol published by Cattamanchi , et al (58) or an updated method if available at the time of analysis. Recrudescent infection will be defined as a PCR product from the failure day that is within 10 base pairs (bp) of a PCR product present on the initial day of infection. A new infection will be defined as a PCR product that is more than 10 bp different in size from the strain(s) present during the initial infection. Others will be labeled as indeterminate and may be investigated further.

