## Final Analysis Plan

The final analysis of the primary objective will be a comparison of incidence rates of malaria treatment episodes per year of follow-up (not including the first infection occurring at enrollment) in each arm of the study. The rates and 95% confidence intervals will be calculated using Poisson distribution. Reported antimalarial drug use without documented positive malaria smear will not count as a malaria treatment episode. Malaria episodes treated with non-study medicines at Queen Elizabeth Central Hospital with verified positive malaria smears will be counted as malaria treatment episodes, and any such treatments will be compared among groups to rule out bias due to different rates of non-study treatment. Withdrawal of participation is described above and includes participants who miss ≥ 2 consecutive routine follow-up visits. For the primary study endpoint, follow-up time for participants while they are enrolled in the study will be included in the analysis. For participants who were withdrawn after missing > 2 consecutive follow-up visits, time after the last visit will be censored from incidence analysis.

Drug efficacy for the first and subsequent episodes of malaria will be compared using Kaplan-Meier 28-day survival estimated and compared using Cox proportional hazards regression. Per-protocol analysis will be used to compare treatment efficacy, with data excluded from treatment episodes for which treatment outcome cannot be determined. Survival analysis will also be used to assess time to first resistant infection in each arm. Categorical data including episodes of liver, kidney or neurological toxicity and presence of anemia will be compared using 2 analysis. Logistic regression will be used to adjust for covariates.

Survival analysis will be used to assess the role of travel outside of Blantyre and bed net use on the risk for malarial and time to first malaria episode. This analysis will be conducted both with and without the inclusion of treatment arm as a covariate in the analysis.

Data will be entered in to the database on the computers at the field site. On a daily basis, the data will be transferred via the internet to the EMMES corporation web-based system.

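### Section 4.3 scores parasitologic outcome on the day-28 smear alone, so an afebrile day-14 or day-21 parasitemia genotyped as recrudescent can still count as an adequate response

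*Protocol*

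**What the plan says.** Section 4.3 (Definition of treatment outcomes) adopts the 2004 WHO classes and writes them out. Late parasitologic failure is "Presence of parasitemia on day 28 without fever" in a child with no earlier early treatment failure or late clinical failure. ACPR is "absence of parasitemia on day 28" "and without previously meeting any of the criteria of early treatment or late clinical failure". Late clinical failure covers days 4 to 28, but parasitemia counts only with danger signs, severe malaria, measured fever or a "history of fever within the past 24 hours in the presence of parasitemia during days 4-28".

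The Follow-up section of the Study Schedule says "Visits will occur on days 1, 2, 3, 7, 14, 21, 28", with a smear and a filter paper at each visit. Section 8.4 (Molecular analysis) says "Cases of parasitemia from day 14 through day 28 will undergo MSP-2 genotyping", and "Recrudescent infection will be defined as a PCR product from the failure day" that lies within 10 base pairs of a product present at the start of the infection.

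For first administration, section 3.2.2 lists two outcomes: the 28-day ACPR rate, and the incidence of new and recrudescent infections. It repeats both for later episodes. The Protocol Summary plans PCR-corrected 28-day efficacy for every treated episode. Section 11.3 says that efficacy "will be compared using Kaplan-Meier 28-day survival estimated and compared using Cox proportional hazards regression".

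**The concern.** Sections 4.3 and 8.4 treat the same smear differently. Section 8.4 calls the day of the recurrent sample the failure day and may label the parasites recrudescent. Under section 4.3, an afebrile day 14 or day 21 can never be a failure day, and nothing that happens then stops the child from becoming an ACPR.

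PCR correction does not clearly bridge the gap. As usually understood, it acts on children already scored as failures and sets aside those whose parasites are new. That cannot turn a responder into a failure, and no section says that a recrudescence before day 28 overrides an ACPR.

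At stake is the meaning of the efficacy rate in secondary objectives 1 and 2. A parasitologic response rate that includes genotyped recrudescences overstates cure, and it disagrees with the recrudescence outcome reported beside it. The survival analysis has a related gap: if its events are taken from the section 4.3 classes, an afebrile failure cannot exist before day 28, whatever the earlier smears showed.

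**Working it through.** The protocol states no figure to reproduce here, so the check applies the section 4.3 rules to every possible course.

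**Inputs.** Smears on days 7, 14, 21 and 28 (Follow-up). A child with no early treatment failure and, at each positive smear, no fever, fever history, danger sign or severe malaria (otherwise the child is a clinical failure under 4.3). Genotyping from day 14 to day 28 (8.4).

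**Step 1: classify.** Four smears, each positive or negative, give 2 × 2 × 2 × 2 = 16 patterns.

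| Smear pattern | Patterns | Class under 4.3 | In the 8.4 genotyping window |
|---|---|---|---|
| All negative | 1 | ACPR | nothing to genotype |
| Positive on day 7 only | 1 | ACPR | no |
| Positive on day 14 and/or 21, negative on day 28 | 6 | ACPR | yes |
| Positive on day 28 | 8 | late parasitologic failure | yes |

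Eight patterns are ACPR. Seven of these contain a positive smear, and six contain one that section 8.4 would genotype. The genotype does not enter the section 4.3 rule, so all six stay ACPR whatever it shows.

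**Step 2: size.** The documents do not say how often this happens. Let x be the assumed share of children with an afebrile recrudescence on day 14 or 21 and a negative day-28 smear. If ACPR as written is 99%, counting these children as failures gives 99% − x.

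| Assumed x | Children per 160 | Children per 120 | ACPR after recount |
|---|---|---|---|
| 0% | 0 | 0 | 99% |
| 2% | 3.2 | 2.4 | 97% |
| 5% | 8 | 6 | 94% |
| 10% | 16 | 12 | 89% |

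One child is 1/160 = 0.6 points, or 1/120 = 0.8 points. The 99% comes from the 2005 pilot in the Background section: 79 of 80 evaluable chloroquine children (98.75%), with one early failure and no late failures. With chloroquine working that well, x should be close to zero at the start. It can rise if resistance emerges with repeated use.

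**The case against.** The strongest defence is that section 4.3 follows a stated convention. It attributes its classes to the 2004 WHO definitions, and section 3.2.2 says that the main interest is clinically apparent efficacy. On that view, ACPR and recrudescence are two measures of different things. This stands in part: the WHO source is not at hand, so no departure from it can be alleged, and the day-28 class is legitimate as a reported outcome. It does not explain how a smear can be a failure day in 8.4 and no failure in 4.3, or how the PCR-corrected figure is to be formed.

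Four stronger readings are tempting, and the documents do not support them.

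- A reader might infer that early afebrile recurrences are thrown away. They are not. Section 3.2.2 reports recrudescent infections and pfcrt 76T in recurrent parasitemia separately, and section 11.3 adds time to first resistant infection.
- A reader might infer that every afebrile failure is dated to day 28. Section 11.3 gives no dating rule, so this is only what follows if the section 4.3 classes are used as they stand.
- A reader might infer that the trial relies mainly on late recrudescence to separate the arms. The Efficacy part of the Background names it as one possibility beside malaria incidence and other longitudinal measures. Section 11.2 already expects little power for day-28 differences at first administration.
- A reader might put a percentage on the misclassified recurrences. With first detection spread evenly over days 14, 21 and 28 and weekly clearance c, the share is [(1 − (1 − c)²) + c + 0]/3, which is 9.7% at c = 0.1 and 27.0% at c = 0.3. No clearance rate is given in the protocol. The model also ignores children who become febrile before day 28, and these are late clinical failures.

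**Conclusion.** The inconsistency is real and follows from the wording alone: section 4.3 can count as a cure a child whom section 8.4 calls recrudescent. This is a stated rule that conflicts with another section, rather than detail left for a statistical analysis plan.

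Its reach is limited. It touches the 28-day efficacy outcomes under secondary objectives 1 and 2, and their survival analysis if that uses the section 4.3 classes. The primary outcome, clinical malaria episodes per year, does not use this definition. The size is unknown; the range in the working rests entirely on assumed values of x. The effect is small while efficacy is near 99% and would matter more if resistance emerged. It is worth correcting because the smears and filter papers are already being collected.

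**What to change.** Reconcile sections 4.3, 8.4 and 11.3 as follows.

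- For the PCR-corrected parasitologic endpoint and the Kaplan-Meier/Cox analysis, count afebrile parasitemia at any visit from day 14 to day 28 as parasitologic failure if it is genotyped as recrudescent.
- Date that failure to the first positive smear.
- Handle new infections on days 14 and 21 in the same way as new infections on day 28, and state that rule once.
- Report the day-28-only class alongside, for comparison with the cited WHO definitions and the 2005 pilot.

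Day 14 is the natural start because genotyping starts there. Day-7 positives can be added only if section 8.4 is extended to genotype the stored day-7 filter papers.

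The change affects scoring only and leaves treatment untouched. With a day-14 start it needs wording but no extra visits, blood samples or genotyping. The cost is a departure from the wording that section 4.3 adopts for this one analysis, and a slightly less favourable efficacy figure.

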### Cases of malaria during follow-up period

If symptomatic malaria recurs within 14 days of the initiation of study treatment, rescue therapy will be given and the episode will be coded as an early treatment failure or late clinical failure. If an illness episode occurs more than 14 days after the initiation of the last treatment, it will be considered to be a new clinical episode and treated with the study drug. The case definition of uncomplicated malaria for new clinical episodes is a positive malaria smear and any of the following signs or symptoms:

- Fever measured at the clinic
- History of fever in the past 24 hours
- Vomiting
- Abdominal pain
- Poor oral intake
- Headache
- Irritability for at least 12 hours

Any participant who has danger signs or signs of severe disease (as described above) including a parasite density greater than 10% or greater than 500,000/mm3 will not be treated with the study drug and will be transported to Queen Elizabeth Central Hospital for further management.

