## Rescue therapy

Rescue therapy will be administered if the participant develops early treatment failure or late clinical failure within the first 14 days after the initiation of therapy. Rescue therapy will be administered according to the national treatment guidelines in Malawi. Participants who develop signs or symptoms of severe malaria, or are deemed too ill to receive oral therapy, will be transferred to the Queen Elizabeth Central Hospital research ward for parenteral therapy.

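### Section 4.3 can class a course as an adequate response although the child was re-treated before day 28 for symptomatic, smear-positive malaria without fever; the rescue rule before day 15 is also worded inconsistently

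*Protocol*

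**What the plan says.** Protocol section 4.3 defines late clinical failure by danger signs, severe malaria, measured fever or "a history of fever within the past 24 hours in the presence of parasitemia during days 4-28". Late parasitologic failure is "Presence of parasitemia on day 28 without fever". Adequate response requires a negative day-28 smear "and without previously meeting any of the criteria of early treatment or late clinical failure". Re-treatment between enrollment and day 28 is not mentioned as a bar.

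Section 7.3.1 decides what is done for a sick child. For symptomatic malaria within 14 days of starting treatment, "rescue therapy will be given and the episode will be coded as an early treatment failure or late clinical failure". For an illness after that, "it will be considered to be a new clinical episode and treated with the study drug". It adds: "The case definition of uncomplicated malaria for new clinical episodes is a positive malaria smear and any of the following signs or symptoms". The list includes measured fever and fever history, but also vomiting, abdominal pain, poor oral intake, headache and "Irritability for at least 12 hours". Any one of these is enough.

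Section 8.2 gives rescue "if the participant develops early treatment failure or late clinical failure within the first 14 days after the initiation of therapy". That ties rescue to the section 4.3 classes. Section 6.7 uses a third wording, clinical treatment failure, for the same 14 days.

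Section 11.3 compares efficacy by Kaplan-Meier and Cox methods on a per-protocol basis, leaving out courses whose outcome cannot be determined. Section 8.4 genotypes parasitemia from day 14 to day 28, and the Protocol Summary promises PCR-corrected 28-day efficacy for each treated episode.

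**The concern.** The group that is treated is wider than the group that can fail. A smear-positive child with headache and no fever on day 21 is ill enough to receive a second full course of study drug, but meets no failure criterion for the first. Old day 28 is then day 7 of the new course. If the smear is negative, section 4.3 credits the first course with an adequate response that the second course produced. If no smear falls on old day 28, the course may be dropped as undetermined. It is a failure in neither case.

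Before day 15 the issue is which rule staff follow. Section 7.3.1 rescues and codes a failure with no stated fever condition. Sections 4.3 and 8.2, taken together, would do neither for a child without fever or danger signs.

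The outcomes at stake are the 28-day response rates after first and later treatments (secondary objectives 1 and 2). If the share without fever is similar across arms, an arm with more recurrences loses more of them from its failure count, which pulls the arms together.

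**Working it through.** There is no stated figure to reproduce; the point concerns rules. First I applied them to one case: a smear-positive recurrence with one non-febrile symptom from the 7.3.1 list and no danger sign.

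| Day of recurrence | Section 7.3.1 | Section 4.3, day 28 negative | Section 4.3, day 28 positive |
|---|---|---|---|
| 10 or 14 | rescue; coded as failure | adequate response | late parasitologic failure |
| 15, 18 or 25 | new episode, study drug; silent on the earlier course | adequate response | late parasitologic failure |
| 28 | new episode, study drug | cannot arise | late parasitologic failure |

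With fever, section 4.3 gives late clinical failure on every one of these days, so the gap is confined to recurrences without fever. On days 10 and 14 the failure labels conflict. From day 15 they do not: section 7.3.1 gives the earlier course no label, and the day-28 smear that section 4.3 relies on has been altered by re-treatment.

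**Size for days 15 to 25.** A child re-treated on day 26 or 27 may still be smear-positive on day 28, so those days are left out. That leaves 11 days.

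Inputs:
- Malaria rate: 1.0 and 1.5 episodes per year (section 11.2), taken as constant over time. Chloroquine's prophylactic effect would lower it early after treatment.
- Share of recurrences without fever or fever history, a: not in the protocol; assumed 10% to 30%.
- Children per arm: 160.

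Share of courses with a recurrence in the window, r = rate × 11/365:
- 1.0 × 11/365 = 3.01%
- 1.5 × 11/365 = 4.52%

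Overstatement of response if all such courses are cleared by day 28, r × a:
- Low: 3.01% × 0.10 = 0.30 points; 160 × 0.0030 = 0.5 children per arm
- High: 4.52% × 0.30 = 1.36 points; 160 × 0.01356 = 2.2 children per arm

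If those courses are dropped instead, the high case, taking these recurrences as the only failures, gives 95.48/(1 − 0.01356) = 96.79% against 95.48%, an overstatement of 1.31 points.

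**Cross-check.** Table 1 in the Background shows no late failures among 80 evaluable chloroquine courses. The exact two-sided 95% upper limit is 1 − 0.025^(1/80) = 4.5%. The range for r is compatible with this, towards its upper end.

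**After PCR correction.** The rate above includes reinfections. If c is the share of recurrences that are recrudescent, the corrected overstatement is r × a × c. The protocol does not give c. With a 99% cure rate reported for chloroquine, most recurrences are likely to be reinfections, so the corrected figure should be well below 0.3 to 1.4 points.

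**The case against.** Several objections carry weight.

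- **The two sections can be partly reconciled.** The symptom list in section 7.3.1 is attached to new episodes, which start after day 14. For the first 14 days the section says only symptomatic malaria and uses failure names defined in section 4.3, so one could read the fever condition into it. This weakens the conflict on days 4 to 14 but does not remove it: no fever condition is stated, section 4.3 itself describes clinical malaria as symptoms with a positive smear, and the rescue trigger is worded differently in 6.7, 7.3.1 and 8.2.
- **The planned analysis is time-to-event and PCR-corrected.** Whether re-treatment is an event or a censoring time could be settled in an SAP, which is not at hand. That is fair for the Kaplan-Meier curves. But the adequate-response rate is itself a listed secondary outcome, section 4.3 fixes its classes, and nothing in 8.4 or 11.3 lets the genotype or the re-treatment override them.
- **The recurrences are not lost.** After day 14 they count in the primary endpoint, those from day 14 are genotyped, and new and recrudescent infections are a separate outcome. This limits the harm, but the response rate is still misclassified.
- **The fever-based classes follow the 2004 WHO definitions.** Widening late clinical failure would reduce comparability, and the protocol warns about judging efficacy on parasites that may not be causing the illness. I accept this; the remedy leaves that class unchanged.

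A reader might infer that large differences between arms would be visibly blunted. That would need something like 15% of courses recurring within the 11 days, which is 0.15 × 365/11, about 5 episodes per year, against 1.5 planned and 2.5 seen historically. The documents do not support such a scenario.

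**Conclusion.** The point holds in a limited form. Taken literally, section 4.3 can award an adequate response to a course that was followed before day 28 by on-protocol re-treatment for symptomatic parasitemia without fever. For days 15 to 27 this is a masking gap, not a contradiction between sections. On days 4 to 14 there is a mismatch over who is rescued and coded as a failure, and its extent depends partly on how symptomatic malaria is read.

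The uncorrected overstatement is about 0.3 to 1.4 percentage points, or 0.5 to 2.2 of 160 first courses per arm. It rests on a constant recurrence rate at the planning values, an assumed 10-30% share without fever, and clearance by day 28. It is smaller after PCR correction.

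A reader might infer that the main result or the DSMB review is compromised. The documents do not support that. A recurrence treated after day 14 counts as an episode in the primary endpoint either way, and an error of this size does not matter against the 75% response level for DSMB discussion when efficacy is expected to exceed 95%. The change is still worth making, because the stated rule misclassifies a treated recurrence and the correction is cheap.

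**What to change.** Keep the fever-based definition of late clinical failure in section 4.3 and add:

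- A course followed by rescue or study drug for smear-positive symptomatic malaria before day 28 cannot be an adequate response.
- In the uncorrected Kaplan-Meier analysis it is an event on the day of re-treatment.
- In the PCR-corrected analysis a recrudescence is a failure and a new infection is censored, both on that day.
- After day 14 the recurrence still counts as a new episode for the primary endpoint.

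Use the section 7.3.1 symptom list with a positive smear as the single rescue trigger for recurrence through day 14, worded identically in 6.7, 7.3.1 and 8.2. Days 1 to 3 should stay under the early-failure criteria, because residual parasites and symptoms are expected then. Report the strict section 4.3 classification as a sensitivity analysis.

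The cost is wording only: symptoms, smears, filter papers and treatment dates are already collected, and genotyping from day 14 is already planned. The downside is slightly less comparability with trials that use the fever-based classes alone, and some low-density parasitemia with non-specific symptoms will count as an event. The sensitivity analysis shows how much that matters.
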